## Abstract

**Background:**

Although older adults are at an increased risk of atherosclerotic cardiovascular disease (ASCVD), the effect of an integrated exercise and cardiovascular health education programme based on self-efficacy theory has not been well investigated among older adults. This study aims at examining the effect of this programme on community-dwelling older adults at risk of ASCVD concerning physical activity level, exercise self-efficacy and ASCVD risk profile.

**Methods:**

A parallel two-arm randomised controlled trial with pretest-posttest design will be performed among 190 Chinese community-dwelling adults aged 60 or above in elderly community centres of the Guangdong-Hong Kong-Macao Greater Bay Area. Eligible participants will be randomised by computerised generation. Experimental group will receive a 12-week integrated exercise and cardiovascular health education programme, which comprises a one-hour group-based health education talk conducted at Week 1, a booklet, a lecture video, a tailor-made exercise video, and a booster intervention by text messaging starting from Week 1 to Week 12. Control group will receive placebo intervention including a talk on basic health issues, a lecture video and corresponding leaflet. The outcomes will be investigated through self-report questionnaires and physiological evaluations at baseline, Week 12, Week 24, and Week 36. Physical activity level, exercise self-efficacy and ASCVD risk profile will be assessed, with physical activity level at Week 24 considered the primary outcome. The main intervention effect (group differences on continuous outcome variables) will be examined via Generalized Estimating Equations with identity link.

**Discussion:**

This study findings will provide clues to the effect of the integrated exercise and cardiovascular health education programme, which is theoretically underpinned with self-efficacy theory, in older adults at risk of ASCVD. It will also enhance the quality of community health education by providing insight into the effective teaching strategies targeting older adults.

**Trial registration:**

This study has been registered on ChinicalTrial.gov (Trial ID: NCT05434273).

## Introduction

Atherosclerotic cardiovascular diseases (ASCVDs), which are cardiovascular diseases caused by plague formation in the arteries, represent approximately 85% of global cardiovascular mortality in 2016 [1]. ASCVDs mainly include coronary heart disease and stroke as they share common aetiologies and risk-enhancing factors including type II diabetes, hypertension, dyslipidaemia, unhealthy diet, physical inactivity, smoking, obesity, and family history [2, 3].

Older adults are exposed to an increased ASCVD risk. Approximately 80% of coronary heart disease mortality in America are older adults while 17% of stroke patients are aged over 85 years [4, 5]. In China, the 10-year ASCVD predicted risk for older adults was projected to be ranged from 5% to 20%, and higher risk was indicated in those with hypertension, diabetes, or smoking habit [6]. Physical activity (PA) is effective in preventing ASCVDs via constraining its risk-enhancing factors including hypertension, diabetes, and obesity [7]. Nonetheless, older adults are the least physically active [7, 8], with less than 60% of them meet the PA recommendation suggested by the World Health Organisation [9]. Hence, it is crucial for healthcare professionals to promote the PA levels of older adults with an ultimate goal to prevent them from developing ASCVDs.

A review of literature identified several studies which examined the effect of various health education programmes in promoting PA among older adults who were at risk of ASCVDs. In these programmes, health information was mostly delivered in a lecture format, accompanied with written materials, i.e. booklet. PA components were also included in previous studies, in which two provided PA advice [10, 11] and six incorporated exercise class in their programmes [12–17]. Supporting strategies such as cardiovascular risk evaluations, motivational strategies or goal setting were also employed [10–14, 16, 17]. These studies had demonstrated positive effects in reducing within-group blood pressure (BP). However, their overall results were not promising as the programme effects on PA level, between-group BP, Body Mass Index (BMI), weight, and waist circumference remained inconclusive [10–13, 15–17]. Moreover, suboptimal attendance rates were common in most studies with exercise classes [12, 13, 15–17]. Resnick et al. [17] revealed that participants were relatively non-adherent to the programme, with merely 33% of participants joined 90% of sessions. For exercise class, the attendance rate for each session was only 60%. Likewise, Amundson et al. [12] and Brokaw et al. [13] demonstrated relatively low attendance rates (14.5 and 13.7 sessions out of 22 sessions respectively). The suboptimal exercise adherence was echoed in a systematic review by Picorelli et al. [18], which indicated that the attendance rates of exercise sessions among older adults ranged from 58% to 77% in five included studies.

A possible reason for the suboptimal exercise adherence is the lack of motivation among older adults. A systematic review by Room et al. [19] revealed that exercise adherence of older adults could be adversely affected by low self-efficacy. Such inference was consistent with another review by Rivera-Torres et al. [20], which stated that self-efficacy played a crucial role in exercise adherence among older adults and suggested to embed the concept of self-efficacy in the design of intervention programmes. However, most existing health education programmes did not aim to enhance the exercise self-efficacy of older adults and did not incorporate self-efficacy theory in the programme development [12, 13, 15, 16]. In fact, increasing number of studies have shown that self-efficacy is a core motivator of PA among older adults [21, 22].

According to Bandura and Adams [23], self-efficacy is defined as a person’s perception in his/her own capability of attaining something successfully [24]. It is postulated that a person with stronger perceived self-efficacy is more likely to perform behaviours needed in attaining specific objectives, and inclines to be more persistent and proactive in overcoming challenges [23]. This concept has been widely applied in studies on cardiac rehabilitation and self-management. The results from these studies have indicated that health education programme based on self-efficacy concept could greatly improve lifestyle and self-care behaviours in older adults [25–27].

Apart from the aforementioned issue, there are several limitations in the existing studies on the health education programme in PA for older adults at risk for ASCVDs. Firstly, these studies were exploratory in nature, with most using either a quasi-experimental or a one group study design [10–14,16, 17]. Secondly, most of them were small-scale, with their sample size ranging from 11 to 46 [10, 14, 17]. Thirdly and perhaps most importantly, some studies only targeted on few risk factors of ASCVDs, for instance, nutrition or PA, and overlooked the fact that the aetiology of ASCVDs is multifactorial [14, 16]. Given the above issues, an integrated exercise and cardiovascular health education programme targeting multiple risk factors, together with increased PA levels based on self-efficacy concept seems to offer a better outcome for older adults at risk of ASCVDs [28]. However, to the best of our knowledge, there are limited studies which examine the effect of such an integrated programme among older adults in terms of their PA levels, self-efficacy, and ASCVD-related outcomes. Hence, more empirical studies are required.

### Theoretical framework

The integrated exercise and cardiovascular health education programme is guided by the self-efficacy theory advocated by Bandura and Adams [23]. In this theory, self-efficacy is a core which affects choice of activities, effort, persistence, and achievement. It is postulated that people with high self-efficacy opt to participate in activities more readily, with greater efforts and longer duration. Four factors are shown to be able to increase self-efficacy: mastering experience, vicarious experience, verbal persuasion, and emotional states [24]. Mastering experience refers to the experience a person attains when taking on a new activity and successfully managing it; while vicarious experience means that observing people similar to oneself succeed strengthens the observer’s beliefs that he or she gets the same capability to master similar activities. In addition, social persuasion emphasizes on positive feedbacks received from others to enhance one’s own belief of success. Emotional states mean that a person experiences sensational change regarding his or her body, and the way this emotional arousal is perceived can influence his or her self-efficacy. Based on this theory, we will incorporate these four components in our integrated exercise and cardiovascular health education programme, thus enhancing older adults’ self-efficacy in engaging in PA (details are shown in the “Materials and methods” section). It is hypothesised that older adults will eventually adopt, maintain, and adhere to PA and other healthier lifestyle behaviours, thereby lowering ASCVD risks.

## Materials and methods

### Study aims

This randomised controlled trial aims to examine the effect of the integrated exercise and cardiovascular health education programme for community-dwelling older adults at risk of ASCVD on PA level, exercise self-efficacy, and ASCVD-related outcomes.

### Study design and setting

The protocol will be reported following the SPIRIT reporting guideline [29]. We will adopt a randomised controlled trial design. This trial will be conducted in urban elderly community centres in the Guangdong-Hong Kong-Macao Greater Bay Area. Fig 1 shows the schedule of enrolment, interventions, and assessments.

**Fig 1 pone.0286181.g001:**
[figure not shown]
Schedule of enrolment, interventions, and assessments. Abbreviations: Two-Minute Walk Test (2-MWT), Body Mass Index (BMI), blood pressure (BP), Chinese version of International Physical Activity Questionnaire (short form) (IPAQ-C, short form), Chinese version of Physical Activity Scale for the Elderly (PASE-C), Chinese version of Self-Efficacy for Exercise (SEE-C).

### Participants

Community dwelling adults will be eligible if they fulfil these inclusion criteria: (1) aged 60 years old or above [30–32]; (2) having at least one ASCVD risk factor, including current smoking, excessive alcohol consumption (daily intake of more than one drink for women and more than two drinks for men), being diagnosed with hypertension, diabetes mellitus or hyperlipidaemia, overweight (BMI which is equal or greater than 25 kg/m^2^), family history of coronary heart disease/stroke or anticoagulant use for ASCVD prevention [1, 33–36]; (3) passing the cardiovascular fitness test; (4) having a mobile and able to read text messages, and (5) able to read Chinese and communicate in Cantonese. However, we will exclude older adults who (1) are visually impaired, hearing impaired, or suffering from any cognitive, psychiatric, or musculoskeletal disorder; (2) have a history of attending any cardiovascular education programme; or (3) have a medical diagnosis of coronary heart disease or stroke.

### Sample size

Taking PA level as the primary outcome, with reference to a meta-analysis by Conn et al. [37], the overall mean weighted effect size of patient education on PA level among 17147 patients with chronically diseases is 0.45. The sample size of the proposed study is calculated via G*Power calculator [38]. For a two-tailed test, with the desired statistical power of 0.80 and significance level of 0.05, the estimated sample size is 158. Although the attrition rates of five related studies were less than 20% [11, 12, 14, 15, 17], for conservative reason, an attrition rate of 20% is assumed. Hence, a total of 190 participants (95 participants per group) will be recruited in the study.

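### The 20% attrition allowance was added to 158 (158 × 1.2) instead of divided out (158 / 0.8), so 190 recruits do not leave the 158 completers that 80% power requires

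*Protocol article*

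**What the plan says.** The Sample size section of the protocol article sizes the trial on physical activity level. The effect size comes from a meta-analysis: "the overall mean weighted effect size of patient education on PA level among 17147 patients with chronically diseases is 0.45". The section then gives the test and the result: "For a two-tailed test, with the desired statistical power of 0.80 and significance level of 0.05, the estimated sample size is 158". It notes that five related studies lost less than 20% of their participants, but chooses the higher figure out of caution and concludes from it: "an attrition rate of 20% is assumed. Hence, a total of 190 participants (95 participants per group) will be recruited in the study".

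The formula for the attrition allowance is not given. The abstract repeats 190, and no other section offers a different basis for it. The section on randomisation sets 1:1 allocation.

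**The concern.** An attrition rate is a share of the people recruited. If 20% are lost, 80% remain, so the number required at the end must be divided by 0.8. The step from 158 to 190 instead adds 20% of the completers. That always gives too small a number, because the loss is then taken from the larger, recruited total.

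The paragraph presents 158, 20% and 190 as one chain of reasoning, and readers will take from it that 80% power survives a 20% loss. If the trial ends with a null result near that loss, the power quoted for it would be slightly too high. The results paper may also carry the same sentence forward.

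**Working it through.** **Inputs, all from the protocol article**

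- Standardised difference d = 0.45, two-sided alpha 0.05, power 0.80, base size 158, attrition 20%, recruitment 190 (95 per group): Sample size section.
- Allocation 1:1: section on randomisation, blinding and concealment.

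**Step 1. Reproduce the base size.** The section names G\*Power but not the test. For a two-sample t-test with n per group, power comes from the noncentral t distribution with 2n − 2 degrees of freedom and noncentrality d × √(n/2).

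| n per group | Total | Power at d = 0.45 |
|---|---|---|
| 78 | 156 | 0.7975 |
| 79 | 158 | 0.8026 |

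The smallest size that reaches 0.80 is 79 per group, 158 in total. This matches the plan exactly. It also confirms that 158 is a requirement for analysed participants, with no spare margin.

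**Step 2. Reproduce the recruitment figure.**

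- Adding 20%: 158 × 1.2 = 189.6, rounded up to 190. This matches the plan.
- Dividing by the retained share: 158 / (1 − 0.20) = 197.5, rounded up to 198 (99 per group). This does not match the plan.

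Of these two calculations, only the first gives 190. The shortfall against the second is 198 − 190 = 8 participants.

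**Step 3. What 190 delivers at 20% loss.**

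- Completers: 190 × 0.8 = 152, or 76 per group. This is 158 − 152 = 6 too few.
- Power at d = 0.45 with 76 per group: 0.787 (noncentral t); the normal approximation gives 0.792.
- Effect detectable with 80% power: 0.457 with 76 per group, against 0.449 with 79 per group.

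**Step 4. What loss 190 can absorb.** 1 − 158/190 = 0.168, so 158 completers remain only if attrition is at most 16.8%.

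**Step 5. Check of the corrected figure.** 198 × 0.8 = 158.4, which covers the required 158.

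**The case against.** The case on the other side does not dispute the arithmetic; it argues that the error hardly matters.

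- **The loss of power is tiny.** It is 80% − 78.7% = 1.3 percentage points against the target. The effect size is less certain than that: with the full 79 per group, moving d from 0.45 to 0.44 already lowers power to 0.785. This stands, and it settles how serious the point is.
- **The 20% is deliberately cautious.** The related studies lost less than 20%, and there is no shortfall at all if loss stays at or below 16.8%. This stands in part. The individual rates are not given, so a rate below 20% need not be below 16.8%. The article also expects absences to rise over four assessments and 36 weeks. The caution that the section claims is the very margin that 190 fails to provide in full.
- **The planned analysis is not a completers-only t-test.** It is a GEE on repeated measurements, adjusted for baseline covariates, and participants with partial follow-up contribute data. The real power may therefore differ from 78.7%. This is fair, but the sizing takes no credit for any such gain and the document gives no figures from which to calculate one, so it cannot support the stated number.

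**Conclusion.** The point holds. The base size of 158 is right. The recruitment figure of 190 does not follow from it at 20% attrition: 198 would be needed. At 20% loss the plan has 152 completers and 78.7% power, not 80%, and it keeps 80% power only up to 16.8% loss.

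These figures assume the two-sample t-test that reproduces the plan's 158, equal loss in the two groups, and an effect of exactly 0.45. They describe the sizing model, not the power of the GEE analysis.

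This is a minor error in consequence. It affects neither the design, the analysis nor the type I error rate. It should still be corrected, because the stated power, attrition and sample size cannot all be true together.

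**What to change.** Correct the last step of the Sample size section in one of two ways.

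1. **Keep 190 and restate what it gives.** Say either that 190 participants provide about 79% power for an effect of 0.45 if 20% are lost (152 completers), or that they provide 80% power with up to 16.8% attrition. This costs one sentence and a slightly less favourable figure. No extra participants are needed and no procedure changes.
2. **Keep both 80% power and 20% attrition.** Recruitment then becomes 198 (99 per group), eight more participants, and the 190 in the abstract changes with it.

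The first option is enough, given the size of the effect. Whichever is chosen, state the attrition formula, so that the step from 158 can be checked and the results paper carries the corrected figure.

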### Randomisation, blinding, and concealment

Following the completion of informed consent and baseline data collection, eligible participants will be allocated into either experimental or control group with 1:1 allocation ratio by a computerised random number generator (Fig 2). The random allocation sequences will be generated by a research assistant not engaging in recruitment. The sequences will be put in sequentially numbered, opaque, sealed envelopes [39, 40]. Research assistants will draw the envelopes in sequence to determine participants’ group allocation. To minimise performance bias, research assistants will not acknowledge participants their group assignment. To avoid contamination, the two groups will receive their corresponding treatments at different times in a private room. In addition, the two groups will undergo data collections at different times. Participants will be instructed not to share their education materials to others following the intervention. To avoid detection bias, the research assistant who performs data collection will be blinded to the group assignment. Since the principal investigator (a nurse) is responsible for conducting the lecture of the experimental group, she is unlikely to be blinded.

**Fig 2 pone.0286181.g002:**
[figure not shown]
Flow diagram of the study. Abbreviations: Two-Minute Walk Test (2-MWT), atherosclerotic cardiovascular disease (ASCVD), Body Mass Index (BMI), blood pressure (BP), Chinese version of International Physical Activity Questionnaire (short form) (IPAQ-C, short form), Chinese version of Physical Activity Scale for the Elderly (PASE-C), Chinese version of Self-Efficacy for Exercise (SEE-C), high-density lipoprotein (HDL), low-density lipoprotein (LDL), short message service (SMS).

### Intervention

#### (1) Experimental group

A systematic review by Peiris et al. includes 11 studies which examined the effect of lifestyle intervention programme integrated with education and unsupervised PA among adults with metabolic syndrome [41]. The intervention period of these studies ranged from 12 to 144 weeks and the duration of at least three months enhanced the outcomes significantly. Hence, the intervention period will last 12 weeks. Participants in the experimental group will receive a self-efficacy-based, integrated exercise and cardiovascular health education programme conducted by the primary research nurse for 12 weeks. The intervention comprising a health education talk, a booklet, a tailor-made exercise video, a lecture video, and a set of one-way text messages is designed based on the self-efficacy theory and is validated by an expert panel which contains two associate professors, one assistant professor, one physiotherapist, one cardiac nurse specialist, one cardiologist and one registered dietitian, with all of whom having considerable experience in conducting studies on lifestyle modification. Contents of the talk are derived from regional and international guidelines on PA recommendation and ASCVD prevention [34, 35, 42–46]. The components of ASCVD prevention are based on the seven predictors of cardiovascular health included in the Life’s Simple 7, a prescription for health formulated by the American Heart Association [42]. While PA will be emphasised in the talk, other elements of ASCVD prevention such as healthy diet, smoking cessation, as well as management on weight, BP, cholesterol, and blood glucose will also be introduced. In Week 1, a nurse will deliver a 60-minute face-to-face health education talk to a group of four to six participants. During the talk, the nurse will educate the participants about the risk factors of ASCVD. Apart from that, each participant will be invited to share his or her experience of performing PA and offer comments to other participants (vicarious experience). During the discussion, the nurse will offer positive feedbacks based on their sharing (verbal persuasion). If the participants raise some negative experience or feelings in relation to PA, suggestions on how they can do PA better will be provided to change their perceptions and feelings (emotional states). In the end, the nurse will demonstrate a set of exercises tailor-made for the elderly and ask the participants to do the return demonstration (mastery experience). These simple exercises are at moderate-intensity and involve an integration of balance training, aerobic and muscle-strengthening activities using a chair and a towel. To fulfil the PA recommendations suggested by the World Health Organisation (a minimum of either 150-minute aerobic PA with moderate intensity or 75-minute aerobic PA with vigorous intensity or a proportional combination of both every week) [7], participants will be encouraged to perform these exercises twice a day, 25 minutes each time in which 5-minute warm-up and 5-minute cool down exercises will be included. To enhance the standardisation of intervention delivery, a tailor-made exercise video, in which a nurse and two elders taking the lead in performing the aforementioned exercises, will be displayed during exercise demonstration (mastery experience and vicarious experience). The exercise video begins with a series of mobility and stretching exercises as warm-up, followed by a series of fitness exercises, including chair aerobics (e.g. hip marching, arm raises, arm swings, and chest expansions), balance exercises (e.g. single-leg stance, and single-leg swings), muscle-strengthening exercises (e.g. sit to stand, calf raises, and leg extension) and towel exercises. The video ends with cool-down exercises which comprise breathing and stretching exercises. To facilitate participants to revise the education materials and practice the exercises at home, each of them will receive a 17-inch portable video player which contains a pre-recorded lecture video (containing the same content as the health education talk) and an exercise video following the talk (mastery experience). On the other hand, a booklet which contains the key points of the health education talk will be provided for the participants as reference (mastery experience). A telephone number will also be provided for the participants in case they have any question or worry regarding the programme (emotional states). To improve exercise adherence, experimental group will be required to document their PA patterns in an exercise log daily.

After the health education talk, a booster intervention will be provided for the participants via short message service (SMS) for 12 weeks to sustain older adults’ motivation in engaging in PA across the study period. Text messaging was adopted in previous behavioural interventions targeting older adults and was shown to have positive outcomes in terms of increased PA and better medical compliance [47, 48]. The SMS we used is one-way as older adults generally consider this communication method to be encouraging and able to remind them important messages [47–49]. As comparable benefits were demonstrated between high-frequency (more than one message per day) and low-frequency messaging (three to five messages per week) [50], it will be appropriate to adopt three messages per week to maintain participants’ motivation while minimising the annoyance of receiving excessive messages. Hence, a total of 36 SMS messages (one message on every Monday, Wednesday, and Friday) will be delivered in the daytime (from 9am to 5pm), according to the participants’ preference. The content of the messages is modified from the study by Müller et al. [47], and will include greeting, instruction/encouragement section and closing. Meanwhile, the message theme is derived from the components of self-efficacy theory including mastering experience, verbal persuasion, and emotional states, with each being used rotationally in each message. The message covers key points of the education talk, encouraging words, reminders, and potential barriers of performing PA and corresponding coping strategies. At Week 7, the participants will receive a SMS message which contains a progress report regarding their interim performance on PA with corresponding advice and feedback (verbal persuasion and emotional states).

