### Data analysis

The data collected will be primarily analysed by SPSS version 26. The baseline demographic and clinical characteristics of the participants in the experimental and control groups will be presented in a table. For continuous variables with normal distribution, the data will be summarised by mean and standard deviation whereas median and interquartile range will be used in the report of continuous data with non-normal distribution. Meanwhile, categorical variables will be summarised for each group by proportion and frequency. With reference to existing studies, age was suggested to be a prognostic factor of PA level, lipid level, weight, and BMI [12–14] while gender might have prognostic importance on PA and lipid levels [12, 14]. Also, hypertension was suggested to be influential to weight [12]. These baseline variables will be regarded as covariates and will be adjusted in the analysis. Meanwhile, as multiple community elderly centres will be involved in the study, centre will also be regarded as a covariate owing to the variations in contextual factors [10].

Generalised estimating equations (GEE), which is an extension of the generalised linear models, is prevalently used in studies with repeated measurements. This semi-parametric method is comparatively flexible in a way that it works with different kinds of data (such as continuous, binary and count data) by applying different link functions [67]. Also, GEE is relatively robust regardless of the choice of working correlation matrix [67]. In this study, for comparing group differences on continuous outcome variables (PA score quantified with PASE-C, exercise self-efficacy score, BP, weight, BMI, waist circumference, fasting glucose, fasting blood lipids, and distance walked), GEE with identity link will be used. For ordinal outcome variables (PA level quantified with IPAQ-C), GEE with cumulative logit link will be used. P-value of less than 0.05 will be regarded as statistically significant. The selection of working correlation matrix will depend on the correlation structure of the observed data. The Quasi-likelihood under Independence Model Criterion (QIC) for the model with each working correlation matrix will be compared and the matrix with the smallest QIC will be preferred [68].

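### The experimental talk is given in interacting groups of four to six, but the sample size assumes independent participants and the analysis as described has no talk-group level, so power and precision may be modestly overstated

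*Protocol article*

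**What the plan says.** Under Randomisation, blinding, and concealment, participants are allocated individually, 1:1. Under Intervention, (1) Experimental group, the Week 1 session is then given in small groups: "a nurse will deliver a 60-minute face-to-face health education talk to a group of four to six participants". The group is part of the mechanism, since "each participant will be invited to share his or her experience of performing PA and offer comments to other participants (vicarious experience"). The Theoretical framework section lists vicarious experience among the four factors that raise self-efficacy.

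Under Sample size, the effect comes from a meta-analysis: "the overall mean weighted effect size of patient education on PA level among 17147 patients with chronically diseases is 0.45". The result is given as: "For a two-tailed test, with the desired statistical power of 0.80 and significance level of 0.05, the estimated sample size is 158". The only further allowance is for dropout: "for conservative reason, an attrition rate of 20% is assumed". This gives 190 recruited, 95 per arm.

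Under Data analysis, GEE is introduced as a method for repeated measurements, with the working correlation chosen by QIC. Age, gender and hypertension are covariates, and "centre will also be regarded as a covariate owing to the variations in contextual factors". Talk group is not mentioned in either section. Under (2) Control group, the control talk is face to face, but no group size and no peer discussion are described.

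**The concern.** People treated together in a small group that is meant to influence its members may end up with more similar outcomes than people treated apart. Individual randomisation does not prevent this, because the correlation arises after allocation. Centre as a covariate removes differences between centres. It does not remove similarity among members of one talk group within a centre and arm.

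The robustness of GEE to the working correlation does not help either. Robust standard errors are valid when the declared clusters are independent of each other. If the participant is the cluster, correlation between participants in one talk group is left out. With any positive within-group correlation, confidence intervals would be too narrow, the 5% test would reject too often under the null hypothesis, and the trial would have less power than stated.

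**Working it through.** **1. The plan's own figure.** A two-sample t-test (noncentral t, as in G*Power) with d = 0.45, two-sided 0.05 and power 0.80 gives 79 per arm, 158 in total, with power 0.803. The stated 158 is therefore exactly the result for independent participants, with no allowance for clustering.

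**2. Completers.** 158 × 1.2 = 189.6, rounded to 190. With 20% attrition, 190 × 0.8 = 152 remain, 76 per arm. Power is then 0.787 by noncentral t, or 0.792 by the normal approximation used below. This small shortfall from 80% comes from the attrition arithmetic, not from clustering, so 79% is the baseline for what follows.

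**3. Group size.** At five per talk, 95/5 = 19 experimental groups. Among completers the average is 76/19 = 4. I use m = 4 and m = 5.

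**4. Formulas, clustering in the experimental arm only.**
- Design effect in that arm: DE = 1 + (m − 1) × ICC.
- Ratio of true to naive standard error: R = √((DE + 1)/2).
- Actual type I error of the naive test: 2 × (1 − Φ(1.96/R)).
- Power: Φ(0.45/(R × √(2/76)) − 1.96), where 0.45/√(2/76) = 2.774.

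**5. Worked case, m = 5, ICC 0.05.** DE = 1.20 and R = √1.10 = 1.049. Type I error = 2 × (1 − Φ(1.869)) = 6.2%. Power = Φ(2.645 − 1.96) = Φ(0.685) = 75.3%.

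**6. Range.** The protocol gives no ICC; 0.01 to 0.10 is my assumption.

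| ICC | m | DE | R | Type I error | Power at 152 |
|---|---|---|---|---|---|
| 0 | – | 1.00 | 1.000 | 5.0% | 79.2% |
| 0.01 | 4 | 1.03 | 1.007 | 5.2% | 78.6% |
| 0.01 | 5 | 1.04 | 1.010 | 5.2% | 78.4% |
| 0.05 | 4 | 1.15 | 1.037 | 5.9% | 76.3% |
| 0.05 | 5 | 1.20 | 1.049 | 6.2% | 75.3% |
| 0.10 | 4 | 1.30 | 1.072 | 6.8% | 73.5% |
| 0.10 | 5 | 1.40 | 1.095 | 7.4% | 71.6% |

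If all 158 were evaluable, the m = 5, ICC 0.05 case would have power 76.9%, against 80.7% without clustering on the same approximation.

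**The case against.** The best argument against the point is that the ICC at Week 24 may be small. Group contact is one 60-minute talk in Week 1, and the abstract sets the primary outcome at Week 24. The rest of the programme reaches people individually, through the video player, booklet, exercise log and 36 one-way text messages. One nurse gives all the experimental talks, supported by a standard exercise video, so differences between deliverers do not arise within that arm. This stands as an argument about size: it makes the lower part of the table more plausible, but it does not show that the correlation is zero.

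Secondly, the article does not name the GEE cluster, and a condensed article may leave that to an analysis plan that is not shown. This also stands: participant as the cluster is my inference from the repeated-measures description. The sample size, however, is fixed in the article and reproduces only under independence. An analysis plan can model talk groups only if membership is recorded, and the article does not say that it will be.

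Thirdly, the power formula is unadjusted, and the planned covariates may recover some precision. That could raise power with or without clustering, but it does not by itself remove correlation within talk groups.

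A reader might also infer that both arms are clustered. With groups of five in both arms and ICC 0.10, type I error would be 9.8% and power 65% at 152 completers. The documents do not support taking that as the main case: no control group size is given, and no peer sharing is described there.

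**Conclusion.** The point holds in a conditional and modest form. The plan treats experimental participants in interacting groups but sizes the trial, and as far as described analyses it, as if they were independent. The direction of the error follows for any positive within-group correlation. A reader might go further and conclude that the standard errors are certainly too small; the documents do not establish that, because they give no ICC.

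The loss becomes noticeable at an ICC of about 0.05, where it is roughly 3 to 4 percentage points of power and 1 point of type I error. The result rests on four assumptions: the ICC range, clustering in the experimental arm only, 4 to 5 completers per group, and the participant as the GEE cluster. The case for acting is that the remedy is cheap and that talk-group membership may be lost if it is not recorded at the time.

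**What to change.** - Record a talk-group identifier for each experimental participant, and for each control participant if the control talks are given in groups.
- In the GEE, make the talk group the independent cluster, with visits nested in persons and persons in groups. Control participants who were not grouped form their own clusters. A partially nested model is an alternative.
- Use robust standard errors with a small-sample correction, since there will be only about 19 experimental groups.
- Keep centre as a covariate.
- Restate the power over an assumed ICC range, such as the one above, without enrolling more participants.

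The cost is one extra variable and a changed cluster definition in the model. The downside is slightly wider intervals and a slightly lower stated power.
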